### Ethics and dissemination

This study has been approved by the Hospital’s Medical Science Research Ethics Committee (IRB00006761-M2020022). All participants will provide written informed consent and could withdraw from the study at any time. The results of this study will be disseminated by peer-reviewed and open access publications.

## Discussion

The goal of this study is to evaluate the real-world effectiveness and safety of percutaneous endoscopic decompression surgery versus open decompression and fusion surgery for LSS. Moreover, we also planned to investigate the influence of various factor on clinical outcomes of LSS.

Percutaneous endoscopic decompression is an advanced mini-invasive technique. Sun et al. [14] introduced an interlaminar approach endoscopic decompression technique to treat lumbar central canal stenosis, the primary outcomes of 38 patients was satisfying.

Lee et al. [12] analyzed 213 patients with lumbar canal stenosis or lateral recess stenosis treated by percutaneous endoscopic decompression, the outcomes of 26 months follow-up showed the satisfied rate reached to 93.8%.

However, there have been some concerns about the application of the percutaneous endoscopic decompression for LSS. The first concern is whether the percutaneous endoscopic decompression could provide sufficient decompression without affecting the stability of the operative level. Secondly, whether the percutaneous endoscopic decompression prevents the degeneration of adjacent level. Finally, the recurrence of symptoms its influence factors.

In this study, the dynamic X-ray, CT, and MRI were performed preoperatively and at 3, 12 months follow-up. The instability of operative level will be assessed according to the changes of ROM and VAS (back) [25]. The decompression range and the degeneration grade will be also measured. These will clarify the exact influence of percutaneous endoscopic decompression on the stability of operative level and the degeneration of adjacent level. Furthermore, various influence factors including demographic variables, healthcare variables, symptom related variables, treatment factors, degeneration grade, stenosis grade, decompression range, stability of operative level, and degeneration of adjacent levels were evaluated. The relationship between these various influencing factors and clinical effectiveness will be helpful to solve the controversial issues of percutaneous endoscopic decompression treatment for LSS.

To the best of our knowledge, this is the first prospective, multicenter, large sample study comparing endoscopic decompression and open decompression fusion treatment for LSS which incorporated clinical evaluation, dynamic X-ray, CT, and MRI.

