#### Special measures

The special measures were composed of clinical assessment and radiological assessment.

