### Clinical assessment

Visual analogue score (VAS) [16], Oswestry disability index (ODI) [17], Japanese Orthopaedic Association score (JOA) [18], MacNab criteria, Patient satisfaction, Complications.

VAS divided the degree of pain from 0 to 10. 0 represented no pain, and 10 represented the most pain. VAS was used to evaluate the pain of the back and lower limb separately.

ODI was wildly used to evaluate the limitations of daily activities caused by spinal diseases. The simplified Chinese version ODI was composed of 10 questions, including pain intensity, self-care, lifting, walking, sitting, standing, sleep, sex, social, travel. The score range for each question was 0–5 points. Summarized each question patient answered and converted into a percentage score.

JOA was an effective method to assess lumbar diseases and the recovery of lumbar spine surgery. The simplified Chinese version JOA included five aspects: low back pain (four items), lumbar function (six items), walking ability (five items), social life function (four items), and mental health (seven items). The recovery rate was calculated according to preoperative and postoperative JOA.

MacNab criteria were used to access the overall effectiveness of the surgery, including four grades: excellent, good, fair, poor.

Patient satisfaction was the patient’s subjective impression of surgery, including three grades: satisfied and accept, not satisfied but accept, not satisfied, and not accept.

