#### Secondary outcome measures

The secondary outcome measures are:The score changes between baseline and 3 months, 6 months, 12 months follow up in: JOA, and VAS.The MacNab criteria of 3 months, 6 months, 12 months follow up. The complication rate and patient satisfaction rate before discharged, and at 3 months, 6 months, 12 months follow up.The changes between baseline and 3 months, 6 months, 12 months follow up in: degeneration grade of adjacent level, stenosis grade of operative level, ROM of operative level and adjacent level.The relationship between the exposure measures, special measures and the postoperative clinical outcomes. (SPIRIT 12)

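### A stability factor that contains change in back VAS should not be used to explain clinical outcome, because back VAS is one of those outcomes

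*Protocol article*

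**What the plan says.** Three statements in the protocol article bear on this.

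- **How instability is assessed (Discussion).** "The instability of operative level will be assessed according to the changes of ROM and VAS (back". This is the only place where the article says how instability will be judged. It gives no cut-off and no rule for combining the two changes.
- **How stability is then used (Discussion, same paragraph).** The list of influence factors includes "degeneration grade, stenosis grade, decompression range, stability of operative level, and degeneration of adjacent levels were evaluated". The next sentence states the purpose: "The relationship between these various influencing factors and clinical effectiveness will be helpful to solve the controversial issues".
- **What counts as clinical outcome (Secondary outcome measures).** The list includes "The score changes between baseline and 3 months, 6 months, 12 months follow up in: JOA, and VAS", and also "The relationship between the exposure measures, special measures and the postoperative clinical outcomes".

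The Special measures section puts both kinds of assessment under one label: "The special measures were composed of clinical assessment and radiological assessment". Clinical assessment confirms that back pain has its own score: "VAS was used to evaluate the pain of the back and lower limb separately". That section also shows that ODI has a pain-intensity question among its 10 and that JOA has four low back pain items. Radiological assessment describes a purely radiological measure, ROM by Cobb angle on flexion and extension X-ray. Secondary outcome measures lists change in operative-level ROM as an outcome in its own right.

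**The concern.** Taken together, these statements put change in back VAS on both sides of an analysis: it helps to define the explanatory factor and it is one of the outcomes to be explained. A patient whose back pain worsens is then more likely to be called unstable, and the same worsening is counted as a poor outcome. The resulting association says nothing about segmental motion. Choosing a different cut-off does not remove the overlap, so this is more than an operational detail left to a fuller document.

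At stake is the secondary aim of identifying prognostic factors. A finding that instability goes with worse pain or disability could be taken as evidence about motion when some or all of it comes from the definition.

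**Working it through.** **The plan's own figures.** The article gives no figure on this point. Its only design figure is the sample size, which reproduces. With a difference of 5, SDs of 15 and 10, two-sided alpha 0.05 and power 0.90, n = (1.960 + 1.282)² × (15² + 10²) / 5² = 136.6, rounded up to 137 per group. Then 137 / 0.8 × 1.2 = 205.5, rounded up to 206. Nothing below changes it.

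**Set-up.** All inputs here are assumptions. Changes in ROM, back VAS and ODI are standardised, with higher meaning more motion, more pain and more disability. ROM change is independent of the other two, so motion truly has no effect. The correlation ρ between back-VAS change and ODI change is set at 0.3, 0.5 and 0.7.

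**One rule in closed form.** Call a level unstable if ROM change exceeds +0.5 SD and back-VAS change is worse than average.

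- Share flagged: 0.3085 × 0.5 = 0.154.
- Mean back-VAS change among those flagged: 0.798 SD.
- The overall mean is zero, so the unstable-minus-stable gap on back VAS is 0.798 / (1 − 0.154) = 0.94 SD.
- The gap on ODI is ρ × 0.94, which is 0.28, 0.47 and 0.66 SD for ρ = 0.3, 0.5 and 0.7. At ρ = 0 it is 0.

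**Other rules.** Simulation with 2,000,000 draws; rejection rates are for 480 patients (80% of 600) at the 5% level.

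| Assumed definition of unstable | Flagged | Gap on back VAS (SD) | Gap on ODI (SD), ρ = 0.3 / 0.5 / 0.7 | Rejection rate for ODI, ρ = 0.3 / 0.5 / 0.7 |
|---|---|---|---|---|
| ROM and VAS both above 0.5 SD | about 10% | 1.26 | 0.38 / 0.63 / 0.88 | 68% / 98% / >99% |
| ROM or VAS above 1.25 SD | 20% | 1.02 | 0.31 / 0.51 / 0.71 | 77% / >99% / >99% |
| Sum of the two z-scores, top 20% | 20% | 1.24 | 0.37 / 0.62 / 0.87 | 90% / >99% / >99% |
| ROM alone, top 20% | 20% | 0 | 0 / 0 / 0 | 5% / 5% / 5% |

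At ρ = 0 the ODI rejection rate is 5% under every rule, while the back-VAS gap is still 1.0 to 1.3 SD under each combined rule.

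**Limit of the ROM-only row.** The simulation has a single population, whereas the cohort has two arms, one with pedicle screws and fusion, which would be expected to restrict motion at the operated level. The planning means for 12-month ODI are 20 and 15, a difference of 5 / √((15² + 10²)/2) = 5 / 12.75 = 0.39 SD. If ROM change largely followed treatment arm, a pooled, unadjusted comparison by ROM could show an ODI difference approaching that size although motion had no effect. The zero therefore applies only within arm or after adjustment for arm.

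**The case against.** The best reply is that the article never commits to a composite variable. It gives no cut-off and no and/or rule, and its sentence could mean that ROM and back VAS are examined side by side. The Methods keep them apart: ROM and VAS changes are separate secondary outcomes, the exposure measures contain no instability variable, and both the combined assessment and stability as a factor appear only in the Discussion. The article also condenses a fuller protocol, where the derivation may be settled.

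Much of this stands. The rules in the table are illustrations, and no particular classification can be attributed to the protocol. But the sentence is prospective and names both changes as the basis for judging instability, and nothing limits the stability factor named in the same paragraph to ROM. If side-by-side reporting is meant, one sentence would settle it.

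Two stronger readings are tempting and are not supported.

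- A reader might infer that the study will find instability predictive of disability whatever the truth about motion. The link is definitional only for back VAS. For ODI and JOA it needs a non-zero correlation with back VAS. Shared pain items make that likely, but the article gives no value.
- A reader might infer that the answer to the leading question in the Discussion, whether endoscopic decompression affects stability, is compromised. There stability is an outcome compared between treatments, this circularity does not arise, and ROM alone is already a listed outcome.

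**Conclusion.** The concern holds as a conditional one. If a stability factor that includes change in back VAS is used to explain clinical outcome, as the Discussion's wording allows, its association with back VAS is built in. Under the rules tried, that gap is about 0.9 to 1.3 SD with motion having no effect. The carry-over to ODI is ρ times that gap: roughly 0.3 to 0.7 SD under the simple and-rule for ρ from 0.3 to 0.7, up to 0.88 SD under the other rules, and zero if ρ is zero. The size rests on assumed cut-offs, combining rules and correlations. That back VAS is built into such a factor does not.

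The effect is confined to the analysis of influence factors, a secondary aim. It deserves correction before that analysis is run, but it does not threaten the study's main result.

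**What to change.** State that whenever stability of the operated level is an explanatory factor for VAS, ODI, JOA or another clinical outcome, it will be represented by ROM change on flexion-extension X-ray alone, analysed within treatment arm or adjusted for arm. State also that any measure combining ROM with back pain will be reported only as a descriptive outcome, next to the separate ROM and VAS results, and will not be entered as a predictor of clinical outcome.

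The cost is a sentence or two in the analysis section. The X-rays and ROM measurements are already planned, so no new data are needed. The downside is that the combined assessment cited in the Discussion is no longer available as a predictor. This is a choice about analysis only and does not prescribe a clinical definition of instability.

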### Limitation

The main limitation of this study is that, treatment group in this observational study is clinical routine treatment determined by the shared-decision making between patient and doctor, rather than randomization, which might lead to selection bias. However, the results could be strengthened by the well-designed prospective study, multicenter, large sample size, and the specific inclusion and exclusion criteria [27], and potential confounding factors will be collected for data analysis to minimize the impact of the selection bias.

### Trial status

The protocol was the second version (V2, 2020/06/30). The protocol status was in recruiting status and have not completed, in which the recruitment began on 11 June 2020 and it will be completed on 31 December 2022. (SPIRIT 3).

## Data Availability

Not applicable.

## Abbreviations

LSS: Lumbar spinal stenosis
VAS: Visual analogue score
ODI: Oswestry disability index
JOA: Japanese Orthopaedic Association score
ROM: range of motion
FSU: function spinal unit
CRF: case report form
ResMan: Research Manager
